### Education levels of the practitioners

All the physicians participating in this study as practitioners or researchers are licensed by the Ministry of Health and Welfare of Korea and have at least one year of clinical experience in Korean medicine. These practitioners will be adequately trained so that they closely adhere to the research protocols and are familiar with the research treatment methods. All the taichi educators have been trained as Korean rehabilitation medical trainees or specialists in taichi exercise and have at least one year of taichi experience. Among them, the research director of this study has more than ten years of taichi experience.

### Intervention

At their first visit, patients in both groups will be educated in managing their own blood pressure by restricting salt intake, losing weight, moderating alcohol consumption, exercising, and regulating their diet. Additionally, patients in both groups will be asked not to do any intense exercise that could influence the results of the trial. After this education, the usual care group will self-manage their own blood pressure for 8 weeks.

In addition to self-management, the experimental group will perform taichi as the study intervention. The taichi used in this study is Chen-style 18-form taichi, which will be conducted over two 60-min sessions per week for a total of 8 weeks (80% compliance and more than 13 sessions in total). In each session, patients will perform 10 min of warm-up exercises, 40 min of taichi, and 10 min of cool-down exercises. To maximize adherence to the study protocol, the intervention will mostly be performed in the 6th floor ward at PNUKH. If group sessions are needed, the practitioners can visit external locations. The patients in the experimental group will receive a reference book on taichi that will promote their retention of the exercises. A daily log will record how many exercises each patient has conducted. At weeks 4 and 8, both groups will visit the hospital for an assessment. After treatment, both groups will be monitored for an additional 4 weeks of follow-up.

### Outcome assessment

At the initial screening visit, the CRC will explain the study protocol to the patient. Then, the participants will be asked about their sociodemographic characteristics, including age, gender, occupation, past history, present illness, and medications, at an isolated room for allocation concealment. All adverse events will be recorded, and the practitioners will check the severity of the events and decide the continuance of the trial. Follow-up assessments will be performed once at 12 weeks after the initial screening visit (Table 1, Fig. 1).

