#### Discontinuation and dropout criteria

Participants will be withdrawn from the study:
◦ If they are found to have a previously undiagnosed severe disease after enrollment and before the start of the clinical trial.◦ If they have another disease (except hypertension) that may influence the results of the trial.◦ If they miss two consecutive assessment visits.◦ If they ask to be withdrawn from the trial.◦ If they are lost to follow-up.

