#### Primary outcome measurements

Blood pressure will be the primary outcome of this trial. The CRC will assess the participant’s blood pressure in a stable state using an automatic electronic blood pressure monitor (HBP-1300, Omron Dalian Co., Ltd., China). To obtain accurate data, the measurements will be conducted three times and their mean value will be used as the outcome. Blood pressure will be measured at baseline (assessment 1), prior to each of the visits (assessments 2 and 3), and during the follow-up visit (assessment 4). The primary endpoint is week 8 (assessment 3).

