### Sample size

This study took into account the results of a previous study [18] that used taichi as the main evaluation index. The calculated sample size necessary for the *t*-test was 36 subjects in each group, which was conducted with a G power analysis with an effect size of 0.67, test power of 0.80, and significance level of 0.05. Considering a dropout rate of 10%, we aim to recruit a total of 40 subjects in each group.

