### Statistical analysis plan

Continuous variables will be expressed as mean ± standard deviation, and categorical variables will be expressed as *n* (%). The demographic baseline information (age, gender, occupation, past history, present illnesses, and medications) will be tested using the chi-squared test and independent *t*-test.

As the primary statistical analysis, the effectiveness of taichi will be tested by calculating the differences in the maximum SBP and minimum DBP before (baseline) and after (week 8) treatment for each test subject. Comparisons of the within-group differences will be performed using a paired *t*-test and between-group differences using an independent *t*-test. If the data do not have a normal distribution, they will be tested using a nonparametric test (a Wilcoxon signed-rank test or Wilcoxon rank-sum test).

The heart rate and the body composition of the participants will be tested to verify the effectiveness of taichi by calculating the difference between before (baseline) and after (week 8) the treatment as described above.

The results of the questions regarding the intensity and difficulty of the exercises will be evaluated by the researchers, and the numerical value will be analyzed by a simple descriptive statistical method. We will perform a simple correlation analysis or simple regression analysis to determine whether there is a correlation between the differences in blood pressure and the intensity and difficulty of the exercise as perceived by the experimental group.

Information regarding adverse events will be collected through patient reports and researchers’ observations. The frequency of adverse events will be analyzed by a chi-squared test or Fisher’s exact test.

All statistical analyses will be conducted in a two-sided manner, with a significance level of 5%. In addition, we will use an intention-to-treat analysis for missing data in the primary and secondary analyses. The last-observation-carried-forward and multiple imputation, which are widely used in clinical research, will be applied to missing data and additional multiple imputation or regression analysis will be used to check any differences.

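### The protocol does not separate stopping taichi from leaving the trial, so a randomized patient removed for another disease, and probably one stopped after an adverse event, may have a measurable week-8 blood pressure imputed

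*Protocol article*

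**What the plan says.** All references are to the protocol article.

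- **Outcome assessment**, on adverse events: "All adverse events will be recorded, and the practitioners will check the severity of the events and decide the continuance of the trial". What is to continue is not defined. It could be the whole trial, one patient's participation or the taichi sessions.
- **Discontinuation and dropout criteria**: the list opens with "Participants will be withdrawn from the study" and offers no other form of stopping. One ground is "If they have another disease (except hypertension) that may influence the results of the trial". The ground just before it is limited to the time before the trial starts; this one carries no time limit. Adverse events as such are not listed.
- **Intervention**: "At weeks 4 and 8, both groups will visit the hospital for an assessment".
- **Primary outcome measurements**: blood pressure is primary, with week 8 as the primary time point.
- **Statistical analysis plan**: "we will use an intention-to-treat analysis for missing data in the primary and secondary analyses", and "The last-observation-carried-forward and multiple imputation, which are widely used in clinical research, will be applied to missing data". Further multiple imputation or regression is to check for differences.
- **Sample size**: "Considering a dropout rate of 10%, we aim to recruit a total of 40 subjects in each group".

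**The concern.** A patient can stop the intervention and still be measured. An intention-to-treat comparison depends on keeping those two things apart, because a measured week-8 value needs no assumption about what happened after the stop, while an imputed one does. LOCF assumes no further change. Multiple imputation within arm (an assumption here, since the protocol does not specify the model) assumes change like that of the rest of the arm. A second imputation method can show that the answers differ, but it cannot recover the reading.

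The withdrawal ground for another disease, followed as written, takes a randomized patient out of the study. The adverse-event sentence may do the same. That decision lies with practitioners who are told the allocation (Randomization). They see taichi patients twice a week, whereas usual-care patients are scheduled only for assessments at weeks 4 and 8 (Intervention). Stops could therefore fall more often in the taichi arm, so the question is more one of bias than of power.

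**Working it through.** **1. The texts side by side.** The adverse-event sentence is about the severity of individual events and is addressed to practitioners. The Safety section gives review of the study's progress to the data monitoring committee. One patient's participation is thus the most natural object of the decision, though not the only one. The withdrawal list is firmer: its ground of another disease is mandatory, undated and ends in withdrawal from the study. The week-4 and week-8 schedule covers both groups but does not say that a withdrawn patient still attends. Intention-to-treat is invoked for values already missing and does not secure their collection.

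**2. The plan's own figure.** Inputs from Sample size and Statistical analysis plan: effect size 0.67, power 0.80, two-sided 5%, *t*-test. The noncentral *t* calculation gives 35.96, so 36 per group, as stated. Then 36/0.9 = 40, so the dropout allowance is 4 per group.

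**3. How far the two imputation methods can differ.** No stopping rate is given, so these inputs are assumed:
- *k* = 1, 2 or 4 stopped patients of 40 (4 uses the whole dropout allowance and is an upper end);
- the remaining taichi patients gain 0.67 SD over usual care;
- usual care itself improves by *c* SD;
- imputation is within arm.

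For a stop before week 4, LOCF carries the baseline forward (zero change), while imputation gives the arm's mean change, 0.67 + *c*. With stops in the taichi arm only, the gap in the treatment effect is *k*/40 × (0.67 + *c*). For a stop after week 4 with half the change reached (assumed) and *c* = 0, it is *k*/40 × 0.335. With *k* stops in each arm before week 4, it is *k*/40 × (0.67 + *c*) − *k*/40 × *c* = 0.67*k*/40 for any *c*.

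| Gap in SD | *k* = 1 | *k* = 2 | *k* = 4 |
|---|---|---|---|
| Before week 4, *c* = 0 | 0.017 | 0.034 | 0.067 |
| After week 4, half the change reached, *c* = 0 | 0.008 | 0.017 | 0.034 |
| Before week 4, *c* = 0.25 | 0.023 | 0.046 | 0.092 |
| Equal stops in both arms, before week 4 | 0.017 | 0.034 | 0.067 |

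At an assumed SD of change of 10 to 15 mmHg, the first row is 0.17–0.25, 0.34–0.50 and 0.67–1.01 mmHg.

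**4. Which method would be right.** Take *k* = 4 and *c* = 0. LOCF gives 36/40 × 0.67 = 0.603, and imputation gives 0.670. If the stopped patients truly gained nothing, measurement would give 0.603 and LOCF is right. If they gained the full 0.67, measurement would give 0.670 and imputation is right. If they gained half, measurement would give (36 × 0.67 + 4 × 0.335)/40 = 0.6365, and each method misses by 0.0335 SD, in opposite directions. Only the measurement tells these cases apart.

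**5. Power at effect size 0.67, analysing observed values.** 40 v 40: 0.841. 39 v 40: 0.836. 38 v 40: 0.832. 36 v 40: 0.821.

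**The case against.** The strongest reply is that the loss of the endpoint is inferred. A reader might conclude that the protocol removes every patient stopped for an adverse event and leaves week 8 unmeasured. The document does not say so. Adverse events are not a listed ground. The week-4 and week-8 visits carry no condition of being on treatment. Falling short of the session target in the Intervention section is not a ground for withdrawal either, so patients who do little taichi can remain in the trial. The continuance decision could also concern the whole trial or only the exercise. All of this stands, and it limits the adverse-event route to a probable reading.

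It does not answer the ground of another disease. That is a stated rule, not a detail that a condensed article leaves to the full protocol, and it removes a randomized patient from the study. It will not cover every adverse event: the muscular pain that the Safety section foresees is hardly another disease. It would cover an event that reveals one.

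A reader might also take the figures above as a bias. They are gaps between two methods under assumed counts. The scheduled adverse-event checks in Table 1 fall at weeks 4, 8 and follow-up. A stop at the week-4 check leaves a week-4 reading, which points to the smaller gaps, and a stop at the week-8 visit coincides with the endpoint visit. Earlier reports remain possible.

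**Conclusion.** The point holds in a limited form. The withdrawal rule for another disease, as written, and the adverse-event decision, if it concerns one patient's participation, can leave an obtainable primary value to imputation. That the adverse-event decision removes the patient is probable, not certain. The documents show no bias; its size and direction are unknown, and it is probably small. The range of 0.008 to 0.092 SD rests on the assumed 1 to 4 stops, the planned effect of 0.67 SD in those who continue, imputation within arm, and an assumed usual-care change of 0 or 0.25 SD. Power is not the issue: with four taichi values missing it still exceeds the planned 0.80, and the sample size need not change. This is a worthwhile clarification because it is cheap and because no later analysis can replace the missing reading.

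**What to change.** - **Outcome assessment**: replace the decision on continuance by a decision on whether taichi sessions continue (taichi group) and what medical care is needed (either group).
- **Discontinuation and dropout criteria**: limit the ground of another disease so that it does not withdraw a randomized patient whose disease is found after randomization, including one revealed by an adverse event.
- **Both places**: state that such patients stay in the trial and have blood pressure measured at weeks 4, 8 and 12 unless they withdraw consent or cannot be reached.
- **Statistical analysis plan**: state that these values enter the intention-to-treat analysis and that imputation covers only values that could not be obtained.

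The cost is a few sentences, with no new staff or procedure. There will be a few more visits to chase, and some stopped patients will still not attend.

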#### Primary outcome measurements

Blood pressure will be the primary outcome of this trial. The CRC will assess the participant’s blood pressure in a stable state using an automatic electronic blood pressure monitor (HBP-1300, Omron Dalian Co., Ltd., China). To obtain accurate data, the measurements will be conducted three times and their mean value will be used as the outcome. Blood pressure will be measured at baseline (assessment 1), prior to each of the visits (assessments 2 and 3), and during the follow-up visit (assessment 4). The primary endpoint is week 8 (assessment 3).

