## Methods/design

### Study design

The proposed study is a randomized, active-controlled, assessor-blinded, two parallel-armed trial. It will be conducted at Pusan National University Korean Medicine Hospital (PNUKH) in Yangsan, Korea. The study protocol was approved by the institutional review board (IRB) of PNUKH on 16 January 2019 (approval number 2018014) and was registered in the Clinical Research Information Service on 18 March 2019 (KCT0003632). Table 1 is the schedule of enrollment, intervention, and assessments. Table 2 lists all relevant items in the World Health Organization’s trial registration data set.

**Table 1 Tab1:** Schedule of enrollment, intervention, and assessments

Measure	Screening (week 0)	Active treatment								Follow-up (12 weeks after screening)^†^
		Week 1	Week 2	Week 3	Week 4 (visit 1)^†^	Week 5	Week 6	Week 7	Week 8 (visit 2)^†^	
Study agreement	X									
Check for participation in other clinical trials	X									
Sociodemographic characteristics^1^	X									
Taichi exercises		Two sessions per week								
Body composition test	X								X	X
Measurement of vital signs^2^	X				X				X	X
Intensity and difficulty of exercises									X	
Number of taichi sessions attended										X
Adverse events					X				X	X

† ±3 days

^1^Age, gender, occupation, past history, present illness, and medications

^2^Blood pressure (systolic and diastolic), heart rate, and body temperature

**Table 2 Tab2:** All relevant items in the World Health Organization’s trial registration data set

Data category	Information
Primary registry and trial identifying number	Clinical Research Information Service, KCT0003632
Date of registration in primary registry	18 March 2019
Secondary identifying numbers	Not applicable
Source(s) of monetary or material support	Traditional Korea Medicine R&D program of Korea Health Industry Development Institute
Primary sponsor	Woosuk University
Secondary sponsor(s)	Not applicable
Contact for public queries	[name], [name], [contact]
Contact for scientific queries	[name], Department of Rehabilitation Medicine of Korean Medicine, Spine and Joint Center, Pusan National University Korean Medicine Hospital, [name].
Public title	Effects of taichi on grade 1 hypertension: A study protocol for a randomized controlled trial
Scientific title	The Effects of Taichi on Grade 1 Hypertension: Randomized controlled trial

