### Recruitment

Patients will be recruited using advertisements on the bulletin boards of Pusan National University Yangsan Hospital (PNUYH) and PNUKH, at local public health centers, and at other local government offices. Patients who are interested in participating will first be screened to determine their eligibility. Eligible patients will receive an explanation of the study and can voluntarily decide whether they wish to participate. If the patient consents to the study terms, a clinical research coordinator (CRC) will check whether they are suitable in accordance with the inclusion and exclusion criteria. Then, the patient will be assigned randomly to the taichi group or the usual care group. After allocation, the CRC will schedule their treatment procedure. The first participant was enrolled on 17 April 2019.

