### Randomization

A statistician who is not involved in conducting or assessing the clinical trial will generate a randomization sequence using the statistical program SAS®, Version 9.4 (SAS institute. Inc., Cary, NC). Using the sequence, the statistician will prepare 80 sealed envelopes, 40 of which will contain an A and 40 a B based on blocked randomization. Once a participant has signed the informed consent form, the CRC will open the next envelope in the sequence and inform the practitioner of the participant’s assignment to the experimental group or the usual care group (Fig. 1).

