### Blinding

Since blinding of the intervention is impossible, the group allocation will not be concealed and the participants will not be blind. Instead, the outcome assessor and data analyst will be blind to the allocation and they will not participate in recruitment or the intervention. The outcome assessor will assess participants at the study visits. The data analyst will analyze the statistical data to prevent selective reporting of outcome variables. Unblinding will be permitted only when it is necessary to reveal the participant’s allocated intervention, such as in cases of severe side effects, at the discretion of the assessor.

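### The assessor-blinding claim is contradicted by the protocol's own role assignments: the coordinator who opens the allocation envelope is also assigned the primary blood pressure readings

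*Protocol article*

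**What the plan says.** The Study design section states the label: "The proposed study is a randomized, active-controlled, assessor-blinded, two parallel-armed trial". The abstract and the end of the Background repeat it, and the masking entry in Table 2 lists the outcome assessor as blinded.

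The Blinding section sets the conditions: "the outcome assessor and data analyst will be blind to the allocation and they will not participate in recruitment or the intervention". It also says who does the measuring: "The outcome assessor will assess participants at the study visits".

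Other sections describe the CRC's work:

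- Outcome assessment: "At the initial screening visit, the CRC will explain the study protocol to the patient".
- Recruitment: "a clinical research coordinator (CRC) will check whether they are suitable in accordance with the inclusion and exclusion criteria", and later "After allocation, the CRC will schedule their treatment procedure".
- Randomization: "the CRC will open the next envelope in the sequence and inform the practitioner of the participant’s assignment".
- Primary outcome measurements: "The CRC will assess the participant’s blood pressure in a stable state". This section also specifies an automatic electronic monitor, uses the mean of three measurements, and names week 8 (assessment 3) as the primary endpoint.

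Under Secondary outcome measurements, heart rate is taken at the same time as blood pressure.

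**The concern.** Participants cannot be blinded, and the Discussion lists this as a major limitation. Blinding of the person who measures is therefore the main safeguard left for the outcome reading. The Blinding section promises it, but the measurement section gives the primary reading to the role that learns each participant's arm by opening the envelope.

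If the measurement section is what happens in practice, a between-group difference in blood pressure is open to detection bias, and so is heart rate. Readers of the abstract or the registry entry would credit the trial with a protection that its own procedures do not secure.

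**Working it through.** **1. The roles side by side.** This part needs no arithmetic.

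| Condition on the outcome assessor (Blinding) | What the CRC does | Where | Compatible? |
|---|---|---|---|
| Does not know the allocation | Opens the envelope and passes the arm to the practitioner | Randomization | No |
| Does not know the allocation | Schedules treatment after allocation | Recruitment | No; only one arm has taichi sessions to schedule |
| No part in recruitment | Explains the study at screening and checks eligibility | Outcome assessment; Recruitment | No |
| Assesses participants at the visits | Measures blood pressure | Primary outcome measurements | Two roles named for one task |

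The envelope is opened at enrolment and the primary reading comes at week 8. The reading that decides the trial is therefore taken after the CRC role has learned the arm. Baseline (assessment 1) is affected only if the envelope is opened before it is recorded. The Randomization section ties opening to signed consent. The Recruitment section puts the suitability check before assignment, and Table 1 places vital signs at screening. The intended order is probably baseline first, but the Randomization wording does not require it.

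**2. The plan's own sample size.** Inputs from the Sample size and Statistical analysis plan sections: d = 0.67, power 0.80, alpha 0.05, two-sided. The two-sample t-test (noncentral t) gives n = 35.96, rounded up to 36 per group, with power 0.8005. With 10% dropout, 36 / 0.9 = 40. Both stated figures reproduce, and this point does not change them.

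**3. Illustration of possible size.** The documents give neither an SD nor a size of bias. Both are assumed here.

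- Assumed SD of change: 12 mmHg. The target difference is then 0.67 × 12 = 8.04 mmHg.
- Standard error at 36 per arm: 12 × √(2/36) = 2.83 mmHg.
- A bias b shifts the t statistic by b / 2.83. The false-positive rate is the probability that |T| exceeds 1.994 (70 df) under that shift.

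| Assumed bias (mmHg) | Share of 8.04 mmHg | Shift in SE | Two-sided error |
|---|---|---|---|
| 0 | 0% | 0 | 5% |
| 1 | 12% | 0.35 | 6.4% |
| 2 | 25% | 0.71 | 10.7% |
| 3 | 37% | 1.06 | 18.2% |

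The result depends on the SD. At a bias of 2 mmHg, an SD of 8 gives 18.2% and an SD of 20 gives 7.0%.

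**The case against.** **Measurement procedure.** The monitor is automatic, and three readings are averaged by rule. The text gives no discretion to repeat or discard a reading. This is a real safeguard against error in reading off the value, and it stands. What it leaves open is the judgement that the participant is in a stable state, which the section does not define.

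**More than one coordinator.** CRC is a role, and the article does not say that one person fills it. A separate coordinator, unaware of allocation, may take the readings. This also stands as a possibility. However, the text speaks of the CRC throughout without distinguishing two people, and one involved in recruitment would still fail the second condition in the Blinding section.

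**A condensed article.** Details left to the full protocol are not a fault. Here, though, the article does state who measures, and it names a role that its own blinding rule excludes. That is a contradiction in what is written, not an omission.

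**The stronger reading.** A reader might infer that the trial is simply not assessor-blinded. The documents do not support that. The Blinding section assigns the visits to the blinded assessor, the measurement section assigns blood pressure to the CRC, and nothing says which governs. The error rates above cannot settle it either, because both of their inputs are assumed.

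**Conclusion.** The protocol contradicts itself on who measures the primary outcome, and the claim of assessor blinding is not secured as written. Following the measurement section puts the week 8 blood pressure, and the heart rate taken with it, in the hands of a role that knows the arm. This conclusion rests on the text alone.

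The size of any resulting bias is unknown. The range of about 6% to 18% for the false-positive rate applies to an assumed bias of 1 to 3 mmHg at an assumed SD of 12 mmHg. It shows only that a bias small relative to the target effect would matter. The sections must be reconciled because this is the primary outcome and participants are necessarily unblinded.

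**What to change.** Reconcile the Recruitment, Randomization, Blinding and Primary outcome measurements sections:

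1. In Primary outcome measurements, replace the CRC with the blinded outcome assessor defined under Blinding, for assessments 2 to 4. Heart rate follows, since it is taken at the same time.
2. State that nobody who opens envelopes or schedules treatment may take those measurements.
3. In Randomization, state that the envelope is opened only after eligibility and baseline blood pressure have been recorded.
4. Disclose any post-randomization readings already taken by a CRC who knew the arm.
5. If the roles cannot be separated, remove the assessor-blinded label from the design description and correct the registry masking entry.

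**Cost.** The Safety section requires modified protocols to go to the IRB for approval, and recruitment is already under way, so this is an amendment during the trial. The site must also confirm that the assessor and the CRC are different people. The Blinding section names the assessor role, but the documents do not show whether a separate person fills it, so extra staff time may be needed. The sample size and the analysis do not change.
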